### Study procedure

2.7

At visit 1, the study clinical researcher will check the participants’ vital signs, medical history, physical examination, algometry pain assessment, the Leeds assessment of neuropathic symptoms and signs (LANSS) pain scale, VAS, the Neuropathy Pain Scale (NPS), functional performance capacity with 6 minutes walking test, the foot and ankle ability measure (FAAM), and laboratory tests (includes, serum HbA1c, and serum albumin levels). The intervention group will received moxibustion management for 30 minutes. In the meantime, the clinical researcher will check the participants’ adverse effects.

From visit 2 to 24 (8 weeks), the intervention group will be treated the same manner as visit 1, and clinical researcher will be check the participants’ algometry pain assessment, the LANSS pain scale, VAS, the NPS, functional performance capacity with 6 minutes walking test, the FAAM, and laboratory tests (includes, serum HbA1c, and serum albumin levels) on visit 12 and visit 24.

At visit 25 (follow-up), the clinical researcher will check the participants’ adverse effects and measured the same manner as visit 12 and visit 24.

If any additional visits may be performed at any time by the clinical researcher's judgment, or following the participant's request. In the event of an unexpected visit, the following tests and assessment will be performed: vital signs, checking adverse events, and laboratory tests. The detailed study period is shown in Table 1.

**Table 1 T1:**
[figure not shown]
The study period of clinical trials.

### Intervention

2.8

#### Intervention group

2.8.1

After randomization, patients of intervention group will receive moxibustion treatment provided by registered physician at TCM Skill Training Centre, Xiamen University Malaysia. The clinical researchers will perform indirect moxibustion on Hegu (LI4), Fenglong (ST40), Quchi (LI11), Sanyinjiao (SP6), Zusanli (ST36), and Taichong (LR3). The treatment session will take 30 minutes per session, and will be done for 3 times per week, lasting for 8 weeks. All moxibustion management was performed by an experienced TCM practitioners in the School of Traditional Chinese Medicine, Xiamen University Malaysia, and also registered practitioners in the Division of Traditional & Complementary Medicine, Ministry of Health Malaysia.

#### Control group

2.8.2

No intervention will be conducted on the control group.

### Outcomes

2.9

#### Primary outcome measure

2.9.1

Pain assessment measured with Algometry: It is used to determine sensitivity to pain produced by pressure.

Pain assessment measured with the LANSS: The LANSS Pain Scale is based on analysis of sensory description and bedside examination of sensory dysfunction, and provides immediate information in clinical settings.^[12]^ The possible scores range from 0 to 24, with a score of ≥12 considered to be suggestive of neuropathic pain.

Pain assessment measured with the VAS: A VAS is a measurement instrument that tries to measure a characteristic or attitude that is believed to range across a continuum of values and cannot easily be directly measured. It is often used in epidemiologic and clinical research to measure the intensity or frequency of various symptoms.

Pain assessment measured with the NPS: Scores are based on patient responses to questions about pain intensity. 0 indicates no pain; 10 indicates the most pain imaginable. The NPS is only for use in patients who have already been diagnosed with neuropathic pain.^[13]^

#### Secondary outcome measure

2.9.2

Evaluation of functional performance capacity with 6 minutes walking test: It is a sub-maximal exercise test used to assess aerobic capacity and endurance. The distance covered over a time of 6 minutes is used as the outcome by which to compare changes in performance capacity. It is plays a key role in measure functional exercise capacity, assessing prognosis and evaluating response to treatment.^[14]^

Evaluation of the FAAM: It is a self-report outcome instrument developed to assess physical function for individuals with foot and ankle related impairments. It is a 29-item questionnaire divided into two subscales: the FAAM, 21-item Activities of Daily Living Subscale and the FAAM, 8-item Sports Subscale. Each item is scored on a 5-point Likert scale (4 to 0) from “no difficulty at all” to “unable to do.” Item score totals which range 0 to 84 for the Activities of Daily Living subscale and 0 to 32 for the Sports subscale were transformed to percentage scores. A higher score represents a higher level of function for each subscale.^[15,16]^

Serum HbA1c: It provides accurate long-term index of average blood glucose level.

Serum albumin levels: It measures the amount of the protein albumin in human blood.

### Safety evaluation

2.10

Study clinical researchers will ask the participants at each visit to identify if they have experienced any adverse effects (AEs). Participants will also be asked to report AEs voluntarily. Any AEs cases will be documented with details on occurrence, duration, severity, and how it is resolved. The case will also be categorized as treatment-related or not treatment-related. Common treatment-related AEs include allergies, burns, infection, coughing, nausea, vomiting, and so on.

### Data collection and management

2.11

Data will be extracted from the online case reports form and questionnaires. All data will be recorded in the online case reports form stored in the TCM Skill Training Center, Xiamen University Malaysia password-protected computer. At least 2 data administrators will log in the information independently and proofread it.

## Data analysis

3

SPSS will be used in statistical analysis. Continuous variable will be shown as mean ± SD, while categorical variables will be shown as percentages and numbers. The significance will be calculated using Student *t* test for matching data or Wilcoxon-test depending on whether normality can be assumed or not. *P* values <.05 will be considered as significantly different.

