**Methods::**

This study will be a pilot, interventional, randomized, 2-armed, parallel, singled-masked, controlled trial. A total of 40 diabetes mellitus patients with peripheral neuropathy will be recruited and assigned randomly into 2 groups (moxibustion group and waiting group) at a 1:1 ratio. This trial consists of an 8-week intervention period and a 4-week follow-up period. During the intervention period, the moxibustion group will take 3 moxibustion sessions per week, whereas no intervention will be done on the waiting group to act as the control group. The outcome will be assessed by an outcome assessor who is unaware of the group assignment. The primary outcome will be pain assessment measured with algometry, Leeds Assessment of Neuropathic Symptoms and Signs pain scale, visual analogue scale, and neuropathy pain scale. The secondary outcome will be an evaluation of functional performance capacity with 6 minutes walking test, evaluation of the Foot and Ankle Ability Measure, and serum HbA1c and albumin levels.

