### Objective

2.1

The main objective of this pilot, interventional, randomized, 2-armed, parallel, singled-masked, controlled trail study is to evaluate the clinical efficacy and safety of moxibustion single treatment in DPN patients.

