### Study design and setting

2.2

This study is designed as a pilot, interventional, randomized, 2-armed, parallel, singled-masked, controlled trial. This study will be conducted at TCM Skill Training Centre, Xiamen University Malaysia from November 2021 to December 2023. A total of 40 diabetes mellitus patients with peripheral neuropathy will be recruited to participate in this trial and will be assigned randomly into 2 groups (moxibustion group and waiting group) at 1:1 ratio. The outcome assessor in this study will be unaware of the group assignments. This trial consists of 8-week intervention period and 4-week follow-up period. The study design is illustrated in a flow chart in Figure 1. Present clinical trial study has not completed participant recruitment at the time of submission.

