### Recruitment and randomization

2.6

Who signed the inform consents participants will be subjected to the measurement of vital signs (eg, blood pressure, pulse rate, and body temperature), demographic information survey, medical history (eg, past, present, and family), and physical examination. Eligible participants who meet the inclusion and exclusion criteria will receive a schedule of clinical trials.

The randomization at a 1:1 ratio into the 2 study arms will be performed via a computer-generated randomization list (prepared by SAS Visual Data science Decisioning, SAS Institute Inc., Cary, NC), which will be kept at the TCM Skill Training Center, Xiamen University Malaysia. Randomization will be stratified by the TCM Skill Training Centre. This computer-generated randomization list show only one result at a time and is unavailable to the enrolling study clinical researcher.

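### The analysis section bases significance on a t test for paired data, or an unspecified Wilcoxon test, and names no explicit between-arm comparison, although the trial randomises independent, unmatched patients to moxibustion or waiting.

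*Protocol article*

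**What the plan says.** The design is stated consistently. Section 2.2 (Study design and setting) says: "This study is designed as a pilot, interventional, randomized, 2-armed, parallel, singled-masked, controlled trial". The same section gives a total of 40 patients who "will be assigned randomly into 2 groups (moxibustion group and waiting group) at 1:1 ratio". Section 2.6 (Recruitment and randomization) adds: "The randomization at a 1:1 ratio into the 2 study arms will be performed via a computer-generated randomization list". Nothing there pairs a moxibustion patient with a waiting patient. The Methods part of the Abstract gives the comparator its role: "whereas no intervention will be done on the waiting group to act as the control group".

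The aim in section 2.1 (Objective) is "to evaluate the clinical efficacy and safety of moxibustion single treatment in DPN patients". Section 5 (Conclusion) expects the controlled trial to settle whether moxibustion works.

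On testing, section 3 (Data analysis) has one sentence. Significance comes from a Student t "test for matching data or Wilcoxon-test depending on whether normality can be assumed or not". The threshold follows: P "values <.05 will be considered as significantly different". No independent-samples test, ANCOVA, mixed model or other between-arm comparison is named in the article.

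**The concern.** A matched t test needs pairs. In this trial the only natural pairs are two measurements on one patient, such as visit 1 and visit 24. Applied as written, the test asks whether patients in an arm changed over time. The objective asks whether they changed more with moxibustion than without it.

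The two questions differ because patients can change for reasons unrelated to treatment: natural course, regression to the mean after selection for having neuropathy, and repeat testing. The waiting group is there so that these shared components can be subtracted. A within-arm P value does not subtract them, so a small P in the moxibustion arm could be reported as efficacy when the waiting group had improved just as much.

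**Working it through.** **Which data could be paired.** Section 2.7 (Study procedure) measures every outcome at visit 1 and again at visits 12, 24 and 25. These are repeated values on the same person. Section 2.6 describes a computer-generated 1:1 list and no matching across arms. A t test for matching data can therefore be applied only to differences within a person, which means within an arm.

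**Inputs for the size of the problem.**
- From the article: 40 patients at 1:1, so 40/2 = 20 per arm; significance level 0.05.
- Assumed, because the article gives none of these: a two-sided test; normally distributed change scores with SD 1 in each arm; no moxibustion effect; the same mean change d (in SD of change) in both arms, with d from 0 to 0.8.

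The article states no power, effect size or SD, so it has no figure of its own to reproduce.

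**Paired test.** The statistic is the mean change divided by (SD of change/√n). It has n − 1 = 19 degrees of freedom, critical value 2.093 and noncentrality d√20:
- d = 0.3: 0.3 × 4.472 = 1.342, probability of P<.05 = 0.247
- d = 0.5: 0.5 × 4.472 = 2.236, probability of P<.05 = 0.565

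**Simulation.** 40,000 trials at each d agree with these values and add the between-arm test. All entries are the share of trials with P<.05 when moxibustion has no effect.

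| Common change d (SD) | Paired test, moxibustion arm | Two-sample test on change |
|---|---|---|
| 0 | 5.1% | 5.1% |
| 0.2 | 13.6% | 5.0% |
| 0.3 | 24.9% | 5.0% |
| 0.5 | 56.3% | 4.9% |
| 0.8 | 92.3% | 4.9% |

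The paired test holds its level only if untreated patients do not change on average. The two-sample test holds it whatever the common change.

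**Baseline adjustment, which bears on the fix only.** With equal variance σ² at both visits and correlation r, the residual variance under ANCOVA is (1 − r²)σ² and the variance of a change score is 2(1 − r)σ². The ratio is (1 + r)/2, which gives 0.75 at an assumed r = 0.5 and 0.85 at r = 0.7.

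**The case against.** The strongest defence is that the article condenses a fuller plan, that a statistical analysis plan may name a between-arm test, and that a parallel controlled trial implies one. This would answer a complaint that something was left out. It does not answer this point, because the article does not leave the t test open: it names a paired one. A later plan with a between-arm test would differ from the published text, which would still need correcting.

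Several stronger readings are tempting, and the text does not support them.

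- **That the article declares a before-versus-after analysis.** Section 3 never says so. It follows by inference, because no other pairs exist. The wording is loose enough that data suited to the test may have been meant, although paired data is the more natural reading.
- **That the Wilcoxon test is certainly paired.** It is not specified. As the alternative to a paired t test it reads as signed-rank, but rank-sum, a valid between-arm test, cannot be excluded. Even then the normal-data branch would remain paired, and the normality judgement would decide which question is asked.
- **That the waiting group would contribute nothing.** This goes too far. The article treats it as the control and may well intend a comparison; section 3 just does not name one.
- **That success will be claimed when moxibustion is significant and waiting is not.** The article states no such rule. In the same simulation that pattern appears in 4.8%, 12%, 19%, 24% and 7% of trials at d = 0, 0.2, 0.3, 0.5 and 0.8, so its frequency does not simply rise with the common change.
- **That failing to adjust for baseline is an error, or that baseline is unused.** A paired test uses baseline by differencing, and an unadjusted between-arm test on change is valid. Covariates are commonly left to a fuller plan.
- **That choosing the test by normality is a fault of similar weight.** It is common practice, and nothing here depends on it.

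It is also fair to object that the error rates depend on an assumed common change. They do, and with no common change they return to 5%. The direction does not depend on the value chosen: any shared non-zero change takes the paired test above its nominal level.

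**Conclusion.** The point holds as a mismatch between a stated test and the stated design. The named t test can assess only within-arm change, no explicit between-arm comparison is given, and the stated aim needs one. It must be fixed.

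Under no moxibustion effect, the false-positive rate for an efficacy claim resting on the moxibustion-arm paired test runs from 5% with no common change to 25%, 56% and 92% at 0.3, 0.5 and 0.8 SD. This assumes normal change scores with equal SD, a two-sided 0.05 level and all 20 patients per arm analysed. The article gives no information on which common change is realistic, so these figures show a range and do not predict this trial's error rate.

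A between-arm test removes the components that both arms share. It does not remove expectation effects, because waiting-group patients know that they are untreated.

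**What to change.** Replace the testing sentence in section 3 along these lines:

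*Each outcome will be compared between the moxibustion and waiting groups, as randomised, at the end of the 8-week treatment period, by ANCOVA with arm and the visit 1 value in the model. The adjusted mean difference will be reported with its 95% CI. A between-arm rank-based analysis (Wilcoxon rank-sum test or rank ANCOVA) will be the sensitivity analysis. Within-arm changes will be described without significance tests.*

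The end of treatment is one reasonable choice of time point; what matters is that one is named in advance. The rank method should be named in full so that it cannot be read as signed-rank. A two-sample test on change would also correct the error. ANCOVA is preferred because visit 1 already measures every outcome, so the variance reduction is free: a factor of 0.75 or 0.85 against change scores at an assumed r of 0.5 or 0.7.

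The cost is one paragraph of text, with no new data, visits or software. Recruitment was not complete when the article was submitted. The correct comparison is more demanding: with 20 per arm, a two-sample t test on change reaches 80% power at a difference of about 0.91 SD, against about 0.66 SD of within-arm change for the paired test. That apparent loss is not a reason to keep the paired test, which answers a different question.

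### The named t or Wilcoxon test gives no between-arm estimate adjusted for the visit-1 value, which usually costs precision at 20 patients per arm

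*Protocol article*

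**What the plan says.** Section 3 of the protocol article is the whole analysis statement. Significance comes from a Student t "test for matching data or Wilcoxon-test depending on whether normality can be assumed or not", and P "values <.05 will be considered as significantly different". It names no covariate and no model, and does not say whether the Wilcoxon test is the signed-rank or the rank-sum version.

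Section 2.7 (Study procedure) lists the visit-1 assessments, beginning with "algometry pain assessment, the Leeds assessment of neuropathic symptoms and signs (LANSS) pain scale, VAS" and going on to the NPS, the 6-minute walk, the FAAM, HbA1c and albumin. The same set is repeated "on visit 12 and visit 24", and visit 25 is "measured the same manner as visit 12 and visit 24". Each primary and secondary outcome in Section 2.9 therefore has one visit-1 value and three later values.

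Section 2.2 (Study design and setting) fixes the size: "A total of 40 diabetes mellitus patients with peripheral neuropathy will be recruited to participate in this trial", "assigned randomly into 2 groups (moxibustion group and waiting group) at 1:1 ratio". Section 2.6 stratifies randomisation only by the training centre, which is the single site, so baseline pain is not balanced by design.

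**The concern.** The trial is randomised so that moxibustion can be compared with waiting. The visit-1 value of an outcome is normally one of the best predictors of its later value, and it is already being collected.

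A t or Wilcoxon test between arms can use it in only two ways. Comparing follow-up scores ignores it. Comparing changes subtracts it with a fixed weight of 1. ANCOVA estimates the weight from the data and is usually more precise than either.

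With 20 patients per arm, a chance difference at visit 1 can be sizeable. It then passes partly into a follow-up comparison, or is over-corrected in a change comparison. At stake are the width of the intervals and the chance of detecting a real effect.

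**Working it through.** **Inputs from the article.** 40 patients at 1:1, so n = 20 per arm; level 0.05 (two-sided assumed, since sidedness is not stated); outcomes at visits 1, 12, 24 and 25. The article gives no power, effect size, SD or sample size derivation, so there is no figure of its own to reproduce.

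**Assumptions.** r between the visit-1 and the later value is 0.3 to 0.7; the SD is the same at both visits and set to 1; the relation is linear; all 40 patients are analysed.

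**Step 1: variance of the between-arm difference.** In units of the follow-up comparison (2/n), follow-up scores give 1, change scores give 2(1 − r), and ANCOVA gives 1 − r². The ratio of ANCOVA to change is (1 − r²) / [2(1 − r)] = (1 + r)/2.

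| r | Change | ANCOVA | ANCOVA / follow-up | ANCOVA / change |
|---|---|---|---|---|
| 0.3 | 1.40 | 0.91 | 0.91 | 0.65 |
| 0.5 | 1.00 | 0.75 | 0.75 | 0.75 |
| 0.7 | 0.60 | 0.51 | 0.51 | 0.85 |

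At r = 0.5, 20 / 0.75 = 26.7 per arm, so 40 patients do the work of about 53. Estimating the slope in a small sample costs a factor of about 1 + 1/(2n − 4) = 37/36. With that factor the figure is 20 / (0.75 × 37/36) = 25.9 per arm, or about 52.

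**Step 2: power for an assumed 0.7 SD effect.** Non-central t with non-centrality 0.7 / √(V × 2/20), where V is the variance factor above. There are 38 degrees of freedom for the unadjusted tests; ANCOVA has 37 and carries the 37/36 factor.

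| r | Follow-up | Change | ANCOVA | Gain over the better unadjusted test |
|---|---|---|---|---|
| 0.3 | 58% | 45% | 61% | 3 points |
| 0.5 | 58% | 58% | 69% | 11 points |
| 0.7 | 58% | 80% | 85% | 5 points |

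A simulation with a normality check choosing the branch (Shapiro-Wilk in each arm; t or Mann-Whitney against ANCOVA or rank ANCOVA; 2,000 trials per setting) agrees. At r = 0.3, 0.5 and 0.7, power over the better unadjusted test rises from 60% to 62%, 57% to 67% and 80% to 85% for normal data. For log-normal data it rises from 80% to 83%, 81% to 88% and 87% to 94%. For normal data r = 0.5 is close to the most favourable case, because follow-up and change scores are then equally inefficient.

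**Step 3: where the gain disappears.** Against follow-up scores, (1 − r²) × 37/36 = 1 at r² = 1/37, so r is about 0.16. Against change scores, (1 + r)/2 × 37/36 = 1 at r = 72/37 − 1, about 0.95. Below the first value or above the second, ANCOVA does not beat the corresponding unadjusted test.

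**Step 4: chance imbalance.** The standard error of a baseline mean difference is √(2/20) = 0.316 SD. The probability of a gap above 0.5 SD is 2 × [1 − Φ(0.5 / 0.316)] = 0.114, or 11% per outcome. A gap g moves a follow-up estimate by r × g and a change estimate by −(1 − r) × g. At g = 0.5 SD and r = 0.5 these are +0.25 and −0.25 SD.

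**The case against.** **The named test is paired, so visit 1 is in use.** A reader might infer that the plan throws the visit-1 value away. The text does not support that. A test for matching data is on its face a paired test. Patients are not matched across arms, so the natural pair is visit 1 with a later visit in the same patient, and the visit-1 value is then half of every difference. This stands. What remains is that a paired difference within an arm is not a comparison of the arms, and Section 3 names no other test that would be one. The precision figures above therefore describe what follows if these tests, or their two-sample forms, are applied between arms on follow-up or change scores.

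**This is efficiency, not error.** A reader might also infer that an unadjusted result would be biased or that its P value could not be trusted. It would not be: over repeated randomisation, unadjusted follow-up and change comparisons are unbiased and hold their level, and chance imbalance is already reflected in their standard errors. This stands in full.

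**Covariates can wait for an analysis plan.** An article that is silent on method could leave this open. Section 3 is not silent: it names tests that cannot take a covariate, so a later ANCOVA would depart from the text rather than fill a gap in it.

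**It is a pilot with no power claim.** True, and r, the 0.7 SD effect and the skewed shape are all assumptions. But Section 2.1 states an efficacy objective and the Conclusion expects the trial to settle whether moxibustion works, so precision matters here.

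**Conclusion.** The point holds as one of precision. The tests named in Section 3 give no between-arm estimate adjusted for the visit-1 value, although the data for one are collected for every outcome. An adjusted comparison would have 0.51 to 0.91 of the variance of a follow-up comparison and 0.65 to 0.85 of that of a change comparison, over an assumed r of 0.3 to 0.7. The power gain over the better unadjusted option runs from a few points at r = 0.3 to about 10 at r = 0.5 for an assumed 0.7 SD effect.

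The direction is dependable over that range. The size is not, because r is not in the document. The change is worth making because it is nearly free, not because the named tests would give a wrong answer.

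**What to change.** In Section 3, compare the arms for each continuous outcome with ANCOVA of the value at a named visit on arm and the visit-1 value of the same outcome. The visit has to be named because three later visits exist; visit 24, the end of the intervention, is one example, with visits 12 and 25 analysed the same way as supportive. Report the adjusted mean difference with its 95% CI for every outcome.

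Where normality is doubtful, keep that estimate, for example with a bootstrap CI, and use rank ANCOVA (Quade's method) for the test in place of the Wilcoxon test. Quade's method alone gives a P value and no effect size, so the estimate should not be dropped in that branch.

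The wording about matching data should be replaced in the same edit. Section 2.7 should state that the visit-1 assessments precede the first session, which at present is only implied by the order in which they are listed.

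The cost is one rewritten paragraph and one degree of freedom per model, with no new data, visits or patients. If r is very low, there is little or no gain.

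### The test for each primary pain scale is chosen by a normality judgement at 20 per arm, so scales can be tested on different hypotheses while all are shown as means; the harm is to interpretation and precision, not to the error rate

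*Protocol article*

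**What the plan says.** The inferential rule is one sentence in the protocol article, section 3 (Data analysis). It gives a Student t test in its matched-data form or a "Wilcoxon-test depending on whether normality can be assumed or not", with P "values <.05 will be considered as significantly different". It names no default test and no criterion for normality. It does not say whether scores or changes are examined, or whether arms are examined separately or pooled. The same section fixes the summary whichever test is used: "Continuous variable will be shown as mean ± SD".

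The rule applies to four primary measures, which the abstract lists as "pain assessment measured with algometry, Leeds Assessment of Neuropathic Symptoms and Signs pain scale, visual analogue scale, and neuropathy pain scale". Section 2.7 (Study procedure) measures them at visit 1, at visits 12 and 24, and again at follow-up: "At visit 25 (follow-up), the clinical researcher will check the participants’ adverse effects and measured the same manner as visit 12 and visit 24". Section 2.2 gives the size, "A total of 40 diabetes mellitus patients with peripheral neuropathy will be recruited", and the allocation, "assigned randomly into 2 groups (moxibustion group and waiting group) at 1:1 ratio".

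**The concern.** Read naturally, whether normality can be assumed is judged once the outcome data exist, and separately for each variable. A t test addresses a mean. A rank test addresses a shift in ranks, or the symmetric centre of paired changes. With a switch, one primary scale may be tested on means and the next on ranks, or one scale may change test between visits. The four results then do not answer one question. Because every continuous variable is shown as mean ± SD, a reader may take a rank P value as a test of the displayed means.

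Twenty values per arm are a weak basis for the judgement. Skew is plausible on at least some scales, since section 2.9.1 bounds LANSS at 0 to 24 and NPS at 0 to 10.

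There is also a loss of precision. The visit 1 score of every scale is collected, but neither branch uses it as a covariate. In a 40-patient trial that is the cheapest precision available.

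**Working it through.** **Inputs from the document.** N = 40 at 1:1, so 40/2 = 20 per arm. Four primary scales. Three assessments after visit 1 (visits 12, 24 and 25). P < .05 for each test. The article gives no effect size, SD or power behind the 40, so there is no stated figure to reproduce.

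**Assumptions not in the document.** Shapiro-Wilk at 5% in each arm, with the rank test used if either arm fails. Two-sided tests. Normal data, or moderately skewed data (gamma, shape 3), scaled to SD 1. True shifts of 0, 0.5 and 0.8 SD. Several thousand simulated trials per scenario, comparing an independent-samples t test with the Wilcoxon rank-sum test.

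**Step 1: how often the switch operates.**
- Normal data: P(at least one arm fails) = 1 − 0.95² = 9.75%; simulated about 10%.
- Gamma(3) data: at least one arm fails in about 61% of analyses, so the t branch is taken in about 39% despite real skew.

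**Step 2: chance that the four scales are not all tested the same way.** With p the chance of the rank branch and scales taken as independent, this is 1 − p⁴ − (1 − p)⁴.
- All normal, p = 0.0975: about 34%.
- All moderately skewed, p = 0.61: 1 − 0.138 − 0.023 = about 84%.

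All four scales measure pain in the same patients, so independence is only a rough guide.

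**Step 3: how often the switch changes a verdict.** The relevant comparison is the switched result against a test named in advance. Shifts are 0.5 to 0.8 SD.

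| Data | Switch differs from fixed t | Switch differs from fixed rank test | t and rank test differ |
|---|---|---|---|
| Normal | about 1% | about 6% | about 7% |
| Gamma(3) | about 8% | about 2% | 10 to 11% |

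The last column is not the effect of the switch. The two tests disagree that often whichever one is fixed.

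**Step 4: error rate and power between arms.** With no true difference, the switched procedure rejects in 4.4 to 5.7% of trials. For gamma(3) data at 0.8 SD, power is about 76% with the switch, 76% with the rank test alone and 70 to 71% with t alone.

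**Step 5: matched changes.** The sentence literally describes paired data. With skewed gamma(3) changes of zero mean, n = 20, rejection is about 6% for t alone and 7 to 8% for both the signed-rank test alone and the switch. A fixed signed-rank test does no better, so the excess comes from the skew and from that test's different target.

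**Step 6: value of the visit 1 score.** A covariate with correlation r multiplies the residual variance by 1 − r², so a 0.8 SD effect behaves like 0.8/√(1 − r²). Power is from the noncentral t with 20 per arm.

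| r (assumed) | 1 − r² | Effective shift | Power |
|---|---|---|---|
| none | 1.00 | 0.80 | 69% |
| 0.3 | 0.91 | 0.84 | 73% |
| 0.5 | 0.75 | 0.92 | 81% |
| 0.7 | 0.51 | 1.12 | 93% |

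The comparator in the first row is an unadjusted two-arm comparison of visit scores.

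**The case against.** Choosing between t and Wilcoxon after a normality check is common practice, and the trial calls itself a pilot. An analysis plan that is not shown may name the check and the variable examined. Against a sensible fixed test the switch changes few verdicts, and it costs no power in the skewed case. Most of this stands, and it limits the point. But a plan that defined the check would still be carrying out a data-dependent rule. That rule is printed here, so this is a badly fixed choice and not merely an omitted detail.

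Three stronger readings are tempting, and the document does not support them.
- A reader might infer that the switch inflates type I error. Between arms it stays near 5%. The 7 to 8% rejection on matched skewed changes should not be charged to the switch, because a fixed signed-rank test gives the same.
- A reader might infer that whoever picks the test can see both P values. The article does not say who analyses the data, whether they are masked, or that both tests will be run.
- A reader might count 4 × 3 = 12 primary analyses. The article lists three assessments after visit 1 but does not say that each is a primary test.

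The missing baseline adjustment is strictly a separate matter from the switch. It belongs here because one replacement sentence settles both.

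**Conclusion.** The point holds as a modest, almost free improvement. Three things follow from the text without simulation: the test may differ between scales or visits, a rank P value may accompany means that it did not test, and the visit 1 score is not used as a covariate.

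The harm is mainly to interpretation and precision. The switch alters roughly 1 to 8% of verdicts, depending on the data and on which fixed test it is compared with, and leaves two-arm type I error essentially intact. These sizes rest on an assumed Shapiro-Wilk check at 5%, 20 patients per arm with no dropout, and shifts of 0.5 to 0.8 SD. An informal judgement of normality would be less reproducible, but its effect cannot be quantified from the article. The power gain depends on a baseline correlation that the article does not give: 4 percentage points at 0.3, 12 at 0.5 and 24 at 0.7.

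Whether a test for matched data compares the randomised arms at all is a different question about the same sentence, and it is not decided here.

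**What to change.** In section 3, delete the normality condition and state one method for all scored outcomes. For example: each scored outcome at each visit will be compared between arms with a linear model that has the visit score as response and arm and visit 1 score as covariates, whatever the observed distribution; the adjusted difference between arms will be reported with its 95% confidence interval. Name a rank or permutation test as a sensitivity analysis that cannot replace the main result.

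Naming either the t test or the rank test in advance would also remove the switch. The model is preferable because it estimates the difference in means that the mean ± SD display implies, and because it uses data already collected.

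The cost is one reworded paragraph, with no further patients, visits or measurements. The change should be made before outcome data are examined.
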